# The Effect of Effort During a Resistance Exercise Session on Glycemic Control in Individuals Living With Prediabetes or Type 2 Diabetes: Protocol for a Crossover Randomized Controlled Trial

**DOI:** 10.2196/63598

**Published:** 2024-11-05

**Keywords:** diabetes, resistance exercise, weight training, glucose, insulin resistance

## Abstract

**Background:**

Type 2 diabetes (T2D) is preceded by prediabetes, and these conditions place a great burden on patients and society. These conditions are significantly associated with poor glycemic control, which is improved by resistance exercise. It has been suggested that resistance exercise should be performed with a high degree of effort to improve glucose metabolism, but this is associated with negative psychological responses that might lead to lower long-term adherence.

**Objective:**

This study aimed to investigate the effect of the degree of effort during a resistance exercise session on glycemic control and psychological responses in individuals living with prediabetes or T2D.

**Methods:**

This study will be a crossover, 3-arm, randomized controlled trial. A total of 15 participants living with prediabetes or T2D will be thoroughly familiarized with 7 resistance exercises; afterward, they will perform 3 randomized experimental sessions, each lasting approximately 48 hours each, separated by at least 4 washout days. In 2 of these sessions, supervised resistance exercise will be performed, but the sessions will differ in the degree of effort in each set (high vs low) and will be equalized in terms of total weight lifted and session duration. For this, proximity to failure will be manipulated by changing the number of sets per exercise, the number of repetitions per set, and the resting interval between sets and exercises. Participants will also complete a sedentary (control) session, where they will not perform any exercise. In response to each session, psychological responses will be assessed (exertion, affect, enjoyment, self-efficacy, and discomfort). Glycemic control will be assessed by a continuous glucose monitoring device every 5 minutes, throughout the approximately 48 hours of each experimental session. Food and drink will be individually prescribed by a registered dietitian nutritionist and provided to participants, in order to control for the confounding effect of energy intake and diet composition. Physical activity levels will be assessed by accelerometry. Randomization will be done using the opaque, sequentially numbered envelopes technique. Participants and researchers will be blinded for continuous glucose monitoring and accelerometry data, and data will be analyzed by a blinded statistician.

**Results:**

This study has been funded, and data collection is expected to take place between June 2024 and May 2025. Final manuscript submission should happen by August 2025.

**Conclusions:**

The results of this project might encourage individuals living with prediabetes and T2D to engage in resistance exercise while better informing exercise specialists on how to best incorporate resistance exercise in their client’s or patient’s routine.

**Trial Registration:**

ClinicalTrials.gov NCT06208189; https://clinicaltrials.gov/study/NCT06208189

**International Registered Report Identifier (IRRID):**

PRR1-10.2196/63598

## Introduction

Type 2 diabetes (T2D) is a disease in which peripheral insulin resistance associated with pancreatic beta-cell dysfunction leads to chronically elevated blood glucose levels [1]. If left unchecked over long periods of time, high glucose levels lead to vascular complications such as increased risk of cardiovascular diseases, diabetic nephropathy, neuropathy, retinopathy, and lower limb amputation [2]. In 2021, a total of 0.7 million people died due to diabetes or its complications in the United States [2], placing diabetes-related deaths as the eighth leading cause of death. T2D is preceded by prediabetes, a condition where blood glucose levels are higher than normal, but not high enough to be considered T2D [3]. The risk of individuals living with prediabetics developing T2D at some point in their life is around 50% [4], and approximately 1 in 3 Americans aged 18 years or older are currently living with prediabetes. The number of people living with diabetes in the United States was 32.2 million in 2021, and it is expected to increase to 36.3 million in 2045 [2]. Diabetes represents a great economic burden to society, as diabetes-related costs in the United States in 2021 were US$ 379.5 billion [2]. Approximately 95% of all diabetes cases are T2D [5].

It is an indisputable fact that exercise is a cornerstone for the prevention and treatment of prediabetes and T2D [6,7]. Of note, even an acute bout of exercise has profound positive effects on glucose metabolism [8]. In fact, exercise training effects on improved insulin sensitivity may be lost in as little as 6 days after the last exercise session in individuals living with T2D [9,10], suggesting the positive effects of exercise on glycemic control can be largely attributed to the acute improvements observed in the hours or days after each exercise bout [11]. Thus, understanding the acute effects of exercise on glucose metabolism is important to optimize exercise prescription for the prevention and treatment of T2D. Although aerobic exercise is usually the default choice for T2D treatment and prevention [7], resistance exercise is also a viable option for physically inactive individuals living with prediabetes and T2D [12,13].

More recently, attention has also been directed to the degree of effort during resistance exercise sets as a potentially important variable that can be manipulated to affect adaptative outcomes [27]. In fact, it has been suggested that a high degree of effort is important for acute improvements in glucose metabolism and insulin sensitivity in individuals living with T2D [28], although direct evidence of that is lacking. In our previous study [24-26], all sets were done with a high degree of effort (perceived exertion 9-10 out of 10 for all working sets). However, performing resistance exercise sets with a high degree of effort is associated with higher perceived exertion and discomfort [29], increased muscle soreness, negative psychological responses [30], and higher neuromuscular fatigue and muscle damage [31]. Taken together, these negative psychological and physiological responses to resistance exercise sets performed with a high degree of effort might negatively affect enjoyment and motivation during a resistance exercise session, which could ultimately reduce long-term adherence [32]. Individuals living with prediabetes and T2D might be more susceptible to these negative responses, as they are more physically inactive than the general population [33] and identify the lack of motivation and low self-efficacy (self-perception of the ability to accomplish something) as barriers to being more physically active [34].

Resistance exercise prescriptions should be tailored to meet not only the glycemic management needs of individuals living with prediabetes and T2D but also their motivation and self-perceived capacity to engage in exercise. Thus, the aim of this study is to assess the effects of the degree of effort during a resistance exercise session on glycemic control and psychological responses in individuals living with prediabetes and T2D. The hypothesis is that the degree of effort will not affect glycemic control, but that a high degree of effort will negatively affect psychological responses.

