### Study Type and Design

This study will be a crossover, 3-arm, randomized controlled trial. The protocol description followed the SPIRIT (Standard Protocol Items: Recommendations for Interventional Trial) [36] and the TiDieR (Template for Intervention Description and Replication) [37] guidelines (Figure 1 and Multimedia Appendices 1-4). Upon meeting eligibility criteria and agreeing to participate, participants will undergo an anthropometrics assessment, familiarization sessions, and strength assessment before randomly carrying out 3 separate experimental sessions (2 exercise and 1 control), with each session taking place over ~48 hours, over 3 consecutive days. The order of the sessions will be randomized and they will be separated by a minimum of 4 washout days.

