### Statistical Analysis

The sample size was calculated using data from relevant literature using similar individuals and glucose-assessing tools (CGM) [11,14,52,53]. Conservative parameters were inserted in the G*Power program (Heinrich-Heine-Universität Düsseldorf, version 3.1.9.6) for a repeated measure ANOVA within interaction: effect size of 0.2 (for 24-hour average glucose concentrations), probability of error type **α** of 0.05, power (probability of error type 1 β) of 0.95, correlation among repeated measurements of 0.7 [54], and nonsphericity correction of 0.5 [55,56]. With these parameters, 15 individuals are required (actual power of 0.96). Considering a typical dropout rate of 25% to 40%, we will initially recruit 25 participants.

A collaborator outside the research team will double-enter data coded for allocation into a computer in separate spreadsheets, allowing the researcher responsible for data analysis to assess the data without access to allocation information. Allocation will only be revealed after statistical analyses are run. In case of doubts about data entry (missing values or values outside the reference range), the researcher responsible for data analysis will contact the collaborator outside the research team responsible for double entry of the data to check accuracy. There will be no interim analysis.

To ensure confidentiality, all study-related information will be securely stored at the study site. All participant information will be kept in locked file cabinets in areas with access controlled by the principal investigator. All laboratory specimens, reports, data collection, process, and administrative forms will be identified by a coded ID number only to maintain participant confidentiality. Records containing names or other personal identifiers, such as locator forms and informed consent forms, will be stored separately from study records identified by code number. No personal information from participants will be released outside the study. Full access to the complete dataset will be restricted to members of the research team.

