The statistical analysis will follow the principles of intention-to-treat analysis [57]. Thus, data from participants will be assessed as randomized, regardless of whether they received the randomized treatment, meaning that even if they fail to follow the physical activity and diet instructions, or fail to complete the sessions as required, their data will be included in the analyses. Furthermore, we will also analyze the data “per protocol” [58], meaning that participants who deviate from instructions will be excluded from the final analyses. Differences in results stemming from intention-to-treat and per-protocol analyses will be discussed accordingly. The available variables will also be compared between participants who withdraw from the study and those who complete the study.

The effect of resistance exercise on glycemic control will be calculated as the absolute and percentage change between control and resistance exercise situations. Data will be expressed as mean and SD, with a 95% CI. For the analysis of data normality, we will perform the Shapiro-Wilk test. For normally distributed data, ANOVA will be used with 1 source of variation (experimental condition). If a significant main effect is observed, the post hoc Tukey test will be conducted. For nonnormal data, the Kruskal-Wallis test or Friedman test will be used as appropriate. The effect size will be calculated and interpreted as follows: <0.2=no effect, 0.2-0.49=low effect, 0.5-0.79=medium effect, and >0.8=large effect [59,60]. The significance level is set at 5%. The Prism program (version 10.1.1, GraphPad Software) will be used to generate graphs and analyze results. This trial will be reported following the CONSORT (Consolidated Standards of Reporting Trials) guidelines [61-63].

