## Discussion

### Potential Impact and Significance of the Study

The results of this study will contribute to a better understanding of the effects of resistance exercise in individuals living with prediabetes and T2D and will be relevant to trainers and therapists who seek to incorporate resistance exercise in their client’s or patient’s routine. Specifically, understanding how short-term glycemic control is affected by altering resistance exercise prescription, in the case of this study, degree of effort, and assessing how this affects psychological responses bears clinical and practical relevance. We anticipate that glycemic control will be similarly improved independently of effort, but participants will experience more positive feelings after the low-effort session. As feelings experienced during a resistance exercise session may be predictive of long-term adherence, this would suggest that correct manipulation of the degree of effort during a resistance exercise session might confer better long-term outcomes for individuals living with prediabetes and T2D.

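### The glycemic hypothesis is that high and low effort do not differ, but the analysis section gives no valid criterion for concluding that they are similar

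*Protocol article*

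**What the plan says.** The Introduction gives the glycemic hypothesis as a null: "The hypothesis is that the degree of effort will not affect glycemic control". The Discussion (Potential Impact and Significance of the Study) repeats it as an expectation, "We anticipate that glycemic control will be similarly improved independently of effort", and derives a practical message: if low effort also feels better, choosing the effort level well may bring better long-term outcomes.

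The Statistical Analysis section then fixes four things.

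- The tests are difference tests at 5%: a one-factor ANOVA on experimental condition, or a rank-based alternative if the data are not normal.
- Pairwise comparison is conditional: "If a significant main effect is observed, the post hoc Tukey test will be conducted".
- The glycemic effect is a contrast with control: "The effect of resistance exercise on glycemic control will be calculated as the absolute and percentage change between control and resistance exercise situations".
- A verbal label is attached to the size of the effect: "The effect size will be calculated and interpreted as follows: <0.2=no effect".

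The sample size of 15 was also obtained from a test of difference, "for a repeated measure ANOVA within interaction". A 95% CI is promised as a descriptive summary, with no decision tied to it. No margin for similarity appears.

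**The concern.** A hypothesis of no difference cannot be supported by failing to find a difference. Absence of significance may reflect similarity or only imprecision, and the planned tests do not separate the two. High versus low effort is the question in the trial's title, yet it is compared only if the three-condition test is significant first. If that test is not significant, the plan names no analysis of the comparison. The below-0.2 label looks only at the point estimate, so an estimate of 0.15 with an interval reaching 0.55 would be called no effect.

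The intended message is that the easier session serves glycemic control as well as the harder one. Under the written plan, results that look favourable to that message could appear when low effort had lost a material part of its benefit.

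**Working it through.** **The plan's own figure.** The Statistical Analysis section gives effect size 0.2 (read as Cohen's f), alpha 0.05, power 0.95, correlation 0.7 and nonsphericity correction 0.5, leading to N = 15 with power 0.96. The numbers of groups and measurements are not stated. By search, 3 groups and 48 measurements reproduce it: λ = 0.2² × 15 × 48 × 0.5 / 0.3 = 48, df = 47 and 282, power 0.956 (47 to 52 measurements also give N = 15). This is power to detect a difference and says nothing about showing similarity.

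**Assumptions for the check.** n = 15 and ρ = 0.7 are the protocol's. I assume f = 0.2 with high and low equal at planning, compound symmetry, and effects in units of the between-participant SD.

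**Assumed exercise benefit.** With condition means (0, δ, δ), f = δ√(2/9), so δ = 0.2 / √(2/9) = 0.424 SD.

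**Precision of high minus low.**

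- SE = √(2 × 0.3 / 15) = 0.200 SD.
- 95% half-width: 2.048 × 0.200 = 0.41 SD (28 df, pooled) or 2.145 × 0.200 = 0.43 SD (14 df, paired).
- 90% half-width, paired: 1.761 × 0.200 = 0.35 SD.
- Expected Tukey critical difference: 3.499 × √(0.3 / 15) = 0.49 SD, larger than the whole assumed benefit of 0.42 SD.

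**Chance of an observed difference within ±0.2 SD.** This is Φ((0.2 − Δ)/0.2) − Φ((−0.2 − Δ)/0.2).

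- Low loses all (Δ = 0.424): Φ(−1.12) − Φ(−3.12) = 0.13.
- Low loses half (Δ = 0.212): Φ(−0.06) − Φ(−2.06) = 0.46.

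**Simulated trials** (ANOVA gate, then Tukey):

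| Truth | Three-condition test not significant | High versus low not declared different | Observed d within ±0.2 | Both beat control, high versus low not significant |
|---|---|---|---|---|
| Low loses all benefit | about 46% | about 63% | 13% | about 1% |
| Low loses half | about 58% | about 91% | 46% | about 7% |

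The third column includes every trial in the second. The 46% agrees with the analytic power of 0.54 for a one-factor, three-condition test at f = 0.2 under sphericity (1 − 0.54 = 0.46).

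**Power to show equivalence** (two one-sided 5% paired tests, n = 15, true difference zero). The protocol gives no margin, so a range is shown:

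| Margin | ρ = 0.7 | ρ = 0.8 | ρ = 0.9 |
|---|---|---|---|
| 0.2 SD | under 0.1% | 0.5% | 10% |
| 0.42 SD | 31% | 59% | 93% |
| 0.5 SD | 54% | 80% | 99% |

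At ρ = 0.7 a margin of 0.6 SD gives 77%; at ρ = 0.5 a margin of 0.5 SD gives 20%. Even if all 25 recruits completed, the 90% half-width at ρ = 0.7 would be 1.711 × √(0.6 / 25) = 0.27 SD, too wide to fit inside ±0.2 SD.

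**The case against.** The strongest defence is that the anticipated message has two parts: exercise improves glycemia, and effort does not change the improvement. Control is the right comparator for the first part, so defining the effect against control is not in itself an error. When the three-condition test fails, no improvement has been shown either, and a claim that low effort works as well would have no basis. On that reading the relevant error rates are about 1% and 7%, not 63% and 91%. This stands for the Discussion's message. The larger figures apply to the bare hypothesis in the Introduction, which does not require improvement over control.

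A reader might infer that the authors will declare similarity from a non-significant test. No sentence says so; the hypothesis is an expectation, not a decision rule. A reader might also infer that the plan can do nothing but fail to reject. That is too strong, since 95% CIs, effect sizes and both intention-to-treat and per-protocol analyses are planned. None of these is tied to a judgement of similarity, so they soften the point without answering it.

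The metric behind the 0.2 cut-off is not stated, nor is it said to apply to high versus low; the 13% and 46% rest on that reading.

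A margin could sit in an analysis plan not shown here, so its absence alone is no fault. The stated gate and label remain, and a later document could not repair them without departing from this text.

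**Conclusion.** The point holds as a mismatch between the hypothesis and the stated inference. The protocol hypothesises no difference and provides no valid way to conclude it. Its only routes to support are a non-significant difference test, possibly never reaching the high-low comparison, and a label that ignores uncertainty.

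Under the assumptions above, the 95% interval for high minus low extends about as far either side of the estimate as the whole assumed exercise benefit. The comparison would be non-significant in about 63% or 91% of trials if low effort lost all or half of its benefit, and the below-0.2 label would apply in about 13% or 46%.

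Two stronger readings are not supported. One is that a noisier trial is always more likely to confirm the hypothesis. This is true of the bare no-effect statement, but noise also hides the exercise-control effect that the improvement claim needs. The other is that 15 participants can never support similarity. At a 0.2 SD margin that is practically so at the protocol's correlation, but a margin of 0.5 SD gives 54% power at ρ = 0.7 and about 80% at ρ = 0.8.

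That the stated N matches a multi-measurement interaction, not the one-factor analysis, is a separate matter and is not needed for this conclusion.

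**What to change.** In the Statistical Analysis section:

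1. Always estimate high minus low in mean glucose with its confidence interval, whatever the result of the three-condition test.
2. Delete the reading of effect sizes below 0.2 as no effect. Name the effect-size metric and report it with its interval.
3. Set and justify a margin in mg/dL before unblinding. Claim similarity only if the 90% CI for high minus low (two one-sided 5% tests) lies inside it, with the already planned per-protocol analysis in support. Otherwise report the comparison as inconclusive.
4. If no margin can be justified, reword the hypothesis and limit the conclusions to estimation.
5. Keep each exercise session versus control as a separate contrast, since the claim of improvement needs it.

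The cost is wording and the choice of a margin; sessions and data collection are unchanged. The downside is that with 15 completers the likely conclusion is inconclusive unless the margin is wide or the correlation exceeds 0.7. For 80% equivalence power at ρ = 0.7, about 22 completers are needed for a 0.5 SD margin, 34 for 0.4 SD and 129 for 0.2 SD.

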## Methods

### Description of Participants

Participants aged between 18 and 75 years will be recruited through posters and flyers at strategic points and by word of mouth in order to support diversity. More specifically, we will recruit from the University of New Mexico’s hospital, clinics, and facilities (both from the Main and North campuses), and from the Albuquerque area in New Mexico. After showing interest, potential participants will be thoroughly informed about the study’s risks and benefits, and they will be asked to answer a medical and physical activity history questionnaire in order to assess eligibility [35]. The inclusion criteria will be presence of prediabetes (fasting glycemia between 100 and 125 mg/dL or glycated hemoglobin [HbA_1c_] between 5.7% and 6.4%) or T2D (fasting glycemia 126 mg/dL or above or HbA_1c_ 6.5% or above), diagnosed by a medical doctor. Glycemic status will be confirmed by assessing a fasting blood sample. Exclusion criteria will be renal failure; liver disease; uncontrolled hypertension (>160 mmHg systolic and/or >100 mmHg diastolic); history of severe cardiovascular problems; inability to perform resistance exercise; being pregnant or trying to become pregnant during the course of the study; use of oral contraceptives; and in case of being treated with biguanides (metformin), being on them for less than 3 months. If eligible, before initiating participation, subjects will sign the informed consent form previously approved by the Institutional Review Board (IRB). Participants will be reimbursed for expenses incurred due to the research and resulting from it. Participation will be discontinued in case of withdrawal of consent or in case of injury or sickness (eg, skeletomuscular injury and having a cold). We will report reasons for withdrawal and discuss the reasons qualitatively. Adverse events related or nonrelated to the research protocol experienced by participants during the study will be carefully recorded and reported in the final manuscript.

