Throughout the entire study period, participants will be explicitly instructed not to alter their prescribed medication and to report any prescription changes made by their medical doctor during participation. Any adverse events whether related or nonrelated to the research protocol experienced by participants during the study (eg, skeletomuscular injury and having a cold) will be carefully recorded and reported in the final manuscript. Figure 2 depicts the study design.

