### Familiarization and Strength Tests

Familiarization and strength tests will be performed as previously described [24-26]. Briefly, familiarization will consist of 5 sessions separated by at least 48 hours. In each session, participants will perform 3 sets of 8-10 repetitions of 7 exercises that target major muscle groups (hex bar squat, seated chest press, leg press, lat pulldown, leg extension, shoulder press, and leg curl; Figure 3), and load will be gradually increased throughout the familiarization sessions so that by the fifth session, participants will be able to perform the exercises with a high degree of effort (9-10 out of 10) based on the OMNI-Resistance Exercise scale [38]. Participants will also be familiarized with the psychological assessments during the familiarization period.

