### Strengths and Weaknesses

This study will take advantage of the latest technology to track glycemic control using a CGM device and accelerometry to directly assess physical activity levels. These are much better approaches compared with other glycemic (handheld glucometers or the oral glucose tolerance test) and physical activity (self-reported questionnaires) assessments, which would increase the reliability of the data as well as its application to real-world scenarios. Also, strict dietary control will be used, and glucose-lowering medication will not be altered, in order to tease out the specific effects of resistance exercise on glycemic control. Finally, a blinded statistician not directly involved in data collection will analyze data, in order to minimize any bias and increase the significance of our findings.

In this study, we will try to anticipate participants’ performance in the high-effort trial by performing a fifth and final familiarization session. This is necessary in case the low-effort trial is randomized to happen before the high-effort one, as the number of repetitions during the low-effort session will be prescribed as half of the high-effort session. However, if the number of repetitions performed in the high-effort session is different from the fifth familiarization session, this could introduce error. Also, to increase the external validity and scope of our results, we will include both male and female participants within a wide age range, as there is evidence that sex and age affect glycemic control [65-74] and response to glucose-lowering drugs [75-79]. Finally, because it has been demonstrated that glycemic control is worsened during the luteal compared with the follicular phase in premenopausal women [80], menstrual cycle phase might be a confounding factor in the present protocol.

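### The stable-medication criterion covers only metformin, so people who recently started or changed another glucose-lowering drug can enter the crossover

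*Protocol article*

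**What the plan says.** All places are in the protocol article.

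- **Description of Participants.** People with prediabetes or T2D are eligible, T2D being defined by glycemia alone ("T2D (fasting glycemia 126 mg/dL or above", or the HbA1c equivalent). No drug class is excluded. The one exclusion about time on treatment is "in case of being treated with biguanides (metformin), being on them for less than 3 months".
- **Study Type and Design.** Participants are told not to change their prescribed medication and "to report any prescription changes made by their medical doctor during participation". Each of the three conditions is run "with each session taking place over ~48 hours, over 3 consecutive days", and "they will be separated by a minimum of 4 washout days". No maximum gap is given.
- **Familiarization and Strength Tests.** Before the first experimental session, "familiarization will consist of 5 sessions separated by at least 48 hours", with a strength test between the fourth and fifth.
- **Statistical Analysis.** The ANOVA has experimental condition as its only source of variation. In the per-protocol analysis, "participants who deviate from instructions will be excluded from the final analyses".
- **Strengths and Weaknesses.** The authors list as a strength that "glucose-lowering medication will not be altered, in order to tease out the specific effects of resistance exercise on glycemic control".

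**The concern.** A crossover compares each person with himself or herself, so its precision depends on underlying glycemia being reasonably steady from one period to the next. The metformin rule suggests that the authors regard a recent start as a threat to that steadiness, but they apply it to one class only. Other therapies are foreseeable: the CGM study described in the Introduction, which is also a source for the sample size, included people on oral agents and people on insulin.

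An unaltered prescription is not the same as a settled drug effect. A drug begun shortly before entry needs no alteration during the study for glucose to keep changing across the three sessions. At stake is within-person precision in a trial of 15. That matters more than usual here because the stated hypothesis is that effort makes no difference to glycemic control. Added noise makes a non-significant high-versus-low comparison more likely, and such a result could be read as support for the hypothesis.

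**Working it through.** The plan gives no figure on this point to reproduce. The check is calendar arithmetic, a comparison of rules, and an illustration on assumed drift.

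**1. Span of the sessions.** Inputs: 3 days per session and at least 4 days between sessions (Study Type and Design).
- Total span: 3 × 3 + 2 × 4 = 17 calendar days.
- From one exercise or control day to the next: 3 + 4 = 7 days; first to third: 14 days.

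**2. Lead-in.** Inputs: at least 48 hours between familiarization sessions, at least 72 hours before and after the strength test, and 72 hours without harder exertion before an experimental session.
- Familiarization session 1 on day 0, session 4 on day 6, strength test on day 9, session 5 on day 12.
- First experimental session starts on day 14 or 15, depending on whether the last 72 hours run to the exercise itself or to instrumentation the evening before.
- Total from first familiarization to last CGM removal: 14 + 17 = 31 to 15 + 17 = 32 calendar days. Three months is roughly 90 days.

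**3. Does another rule close the gap?**
- The no-alteration instruction begins at participation and does not screen out drugs started before it.
- Discontinuation is limited to withdrawn consent, injury or sickness.
- No period term is stated. One would in any case absorb only a trend common to all participants, not drift in a few.

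**4. Illustration of size. The drift and the number affected are assumptions, not figures from the documents.** Let k of 15 participants drift linearly by D between first and third session, with D = 2 weeks × 5 to 15 mg/dL per week = 10 to 30 mg/dL, no allowance for the lead-in, and the six orders equally likely.
- For one such person, the contrast between two given conditions shifts by +D or −D (probability 1/6 each) or by +D/2 or −D/2 (probability 1/3 each).
- Mean shift: 0. Variance: 2 × (1/6) × D² + 2 × (1/3) × D²/4 = D²/2.
- SD of the shift in the group mean: √k × D / (√2 × 15). For k = 1 this is 0.5 to 1.4 mg/dL; for k = 3 it is 0.8 to 2.4 mg/dL.
- Extreme case: k = 3, D = 30, all in the same direction: 3 × 30 / 15 = 6 mg/dL. For a given pair of conditions, all three must have one of them first and the other third, in the same order: 2 × (1/6)³ = 2/216, about 0.9%.

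**5. Effect on the test.** Simulation of a one-way repeated-measures ANOVA with N = 15, effect size 0.2, correlation 0.7, three conditions in random order and no sphericity correction. Drift is in SD units over the three periods.

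| Share drifting | Drift | Type I error | Power |
|---|---|---|---|
| 0% | none | 5.0% | 54% |
| 20% | 0.5 SD | 5.0% | 52% |
| 20% | 1.0 SD | 4.9% | 47% |
| 40% | 0.5 SD | 4.9% | 50% |
| 40% | 1.0 SD | 4.9% | 42% |

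The 54% is only the baseline of this simple model, not a check of the plan's stated power. The change from it is what matters here.

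**The case against.** A reader might infer that drug-driven drift biases the comparison, so that session order could manufacture or hide an exercise effect. The documents do not support this. Order is randomized, so drift unrelated to condition has zero expected effect on every contrast, and simulated type I error stays near 5%. What remains is lost precision and chance imbalance.

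Three further points count against a strong version:
- Nothing shows that any recently treated person will be recruited, and the sample also includes prediabetes. *Can enter* is as far as the text goes.
- The lead-in takes effect off the front. Someone who started a drug a week before the first familiarization session is about three weeks into treatment at the first measurement. Whether glucose is still moving then cannot be read from the documents.
- A reader might also infer that neither analysis set deals with a prescription change ordered by a physician. The article's per-protocol wording does turn on departing from instructions, and a participant who reports such a change has followed them. But the detailed definition of that set may sit in a statistical analysis plan that is not shown, so this is something to confirm, not a defect.

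It can also be said that a metformin window need not suit every agent. That is fair, and it leaves the length of any window to the authors. None of this removes the gap: a stability rule is stated, it covers one class, and nothing else in the article screens for the rest.

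**Conclusion.** The point holds as an eligibility rule drawn too narrowly. People who recently started or changed a glucose-lowering drug other than metformin can enter and could complete the study in about 31 to 32 days. For them, the claim that unaltered medication isolates the exercise effect is not secured.

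The consequence is noise, not bias. Its size cannot be derived from the documents. Under the assumed drift, one to three affected participants would typically move a group contrast by about 0.5 to 2.4 mg/dL in either direction, and 6 mg/dL is a rare extreme. In the simulation, power falls from about 54% to between 52% and 42% if 20% to 40% of participants (3 to 6 of 15) drift by 0.5 to 1.0 SD. These figures rest on linear drift, equally likely orders and no credit for the lead-in. This is a cheap improvement, not a threat to the trial's validity.

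**What to change.** Reconcile Description of Participants with the medication instruction in Study Type and Design and with the claim in Strengths and Weaknesses. The direct way is to extend the stable-medication eligibility criterion to all glucose-lowering drugs, using the protocol's existing 3-month window or another that the authors justify. If they prefer to keep it to metformin, they should say why and qualify the claimed strength.

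As a secondary point, confirm that sessions after a reported change in glucose-lowering prescription are left out of the per-protocol set and kept in the intention-to-treat analysis.

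The cost is one eligibility line and, if it is not already written elsewhere, one line on the per-protocol set, with the ethics submission and registry update that the article requires for any modification. The downside is that some recently treated people must wait or are not eligible. Nobody's treatment changes.
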